### Safety evaluation

Any adverse events or abnormalities will be recorded in the case report forms irrespective of the intervention used. Severity will be evaluated as mild, moderate, or severe, and the relation of any events to the intervention will be evaluated as not related, possibly related, or related.

If any serious adverse events occur, the intervention will be stopped immediately and appropriate action will be taken. This will be reported promptly to the institutional review board, according to the protocol.

### Sample size estimation

DIND, the primary outcome of the trial, was used to calculate the sample size. According to our pilot trial carried out in 2012, the incidence rate of DIND was 10% in the study group and 38.9% in the control group [24]. The difference in the expected incidence rate of DIND between the two groups (P_c_ - P_t_) is therefore 28.9%. To detect this difference with a two-sided 5% significance level and a power of 95%, 39 participants per intervention arm have to be randomized, allowing for a 20% dropout rate [31].$$ n=\frac{{\left({z}_{\alpha /2}+{z}_{\beta}\right)}^2\left({p}_c{q}_c+{p}_t{q}_t\right)}{{\left({p}_c-{p}_t\right)}^2} $$

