## Abstract

**Background:**

Subarachnoid hemorrhage (SAH) is a neurological disease with a high mortality rate. Several serious complications frequently arise after successful surgery for this condition. Cerebral vasospasm, one such complication, occurs in 50 to 70% of SAH patients. These patients suffer neurological symptoms known as delayed ischemic neurological deficit (DIND); however, the effect of treatment of vasospasm is limited. The major pathogenesis of cerebral vasospasm is the reduction of nitric oxide (NO) and activation of vasoconstrictors. Acupuncture is known to increase the production and activity of vascular endothelial cell-derived NO and improve endothelium-dependent vasodilatation. A preliminary retrospective case study to investigate the ability of acupuncture to prevent the occurrence of cerebral vasospasm has been conducted. However, no randomized, controlled clinical trials have been carried out to evaluate the efficacy of acupuncture for cerebral vasospasm.

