## Background

Subarachnoid hemorrhage (SAH) can occur spontaneously or as a result of trauma [1]. The most common cause of spontaneous SAH is aneurysm rupture (about 80% of cases), while vascular malformations, tumors, venous angioma, or infectious aneurysms may also cause bleeding [2,3]. The incidence rate is about 1 per 10,000 people per year, and SAH accounts for about 5% of stroke patients [3,4]. The rate of SAH is low when compared to cerebral hemorrhage or cerebral infarction; however, this condition is a large burden to both individual patients and society because of high mortality rates and treatment costs in neurological intensive care units [5-7].

Treatment of SAH involves early ligation of the aneurysm or insertion of a coil; however, complications such as cerebral vasospasm, rebleeding, or hydrocephalus frequently occur after successful surgery [2-4,7,8]. Such complications increase the mortality rate of SAH or lead to patient sequelae [4]. In particular, cerebral vasospasm is the most serious complication of SAH [9]. It is reported that 23% of the deaths or disabilities that occur as a result of SAH are due to vasospasm [10]. Cerebral vasospasm begins 3 to 4 days after the onset of SAH and reaches a maximum between 7 and 10 days [7,11,12]. Vasospasm occurs in 50 to 70% of SAH patients, and about 50% of these patients suffer neurological symptoms such as deterioration of consciousness and language disorders [3,11,13]. Such symptoms are known as delayed ischemic neurological deficit (DIND). Cerebral infarction occurs in half of DIND patients and a permanent neurological deficit remains in about 35%. In addition, 30% of patients die of DIND [4,7].

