Acupuncture is an effective and safe treatment method that has been used for the treatment of acute stroke including SAH for centuries [17]. In recent years, a number of studies have been published that show that acupuncture increases the production and activity of vascular endothelial cell-derived NO and can improve the function of damaged vascular endothelial cells [18,19]. Acupuncture point ST36 (Zusanli) is known to lower blood pressure and sympathetic nervous tension [18,19]. In particular, it was reported that electroacupuncture stimulation at ST36 lowers blood pressure by increasing the activity of endothelial NO [19]. NO released from endothelial cells plays a key role in maintaining the tension of the vascular wall [20]. Since reduction of NO is the major pathogenesis of cerebral vasospasm after SAH, it can be assumed that acupuncture at ST36 will stimulate the production of NO and normalize endothelial function in patients with SAH. Another acupoint, PC6 (Neiguan), is known to reduce the ischemic heart damage caused by increased myocardial oxygen demand as a result of sympathetic nervous excitement; it also lowers blood pressure and reduces nausea and vomiting [21]. In a study using a finger photoplethysmogram, acupuncture at PC6 was reported to be effective in reducing arterial stiffness in hypertensive patients [22]. Although this study was performed to investigate the acute reaction to acupuncture, it can be assumed that acupuncture at PC6 normalized endothelial cell function and so reduced arterial stiffness.

Based on previous reports, a clinical study was conducted in hypertensive patients with damaged arterial endothelial cell function, which confirmed that acupuncture at ST36-PC6 improved endothelium-dependent vasodilatation [23]. After this, we carried out a preliminary retrospective case study in patients with SAH. The results indicated the possibility of acupuncture treatment in preventing the occurrence of cerebral vasospasm after SAH [24]. To confirm the effectiveness and clinical application of acupuncture for cerebral vasospasm, rigorous clinical trials such as randomized, double-blind trials are required. The aim of this study will be to assess the efficacy and safety of acupuncture treatments in SAH patients for preventing delayed cerebral vasospasm through a randomized controlled trial.

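### The sample size section claims 95% power, but its own formula gives 39 per arm only at 80% power, and even that rests on retrospective rates and a control rate slightly above the Background's range

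*Protocol article*

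**What the plan says.** Under Sample size estimation, the protocol article bases the calculation on delayed ischemic neurological deficit (DIND), the primary outcome. "According to our pilot trial carried out in 2012", it reports, "the incidence rate of DIND was 10% in the study group and 38.9% in the control group", a difference of 28.9 points, citing reference 24. It then states the target: "To detect this difference with a two-sided 5% significance level and a power of 95" per cent, for which 39 per arm are to be randomized after a 20% dropout allowance. It prints an unpooled two-proportion formula. The recruitment target elsewhere is 80 patients in two groups.

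The Background describes the earlier work differently: "we carried out a preliminary retrospective case study in patients with SAH". The next sentence carries the same reference: "The results indicated the possibility of acupuncture treatment in preventing the occurrence of cerebral vasospasm after SAH [24]". The abstract agrees with the Background: "A preliminary retrospective case study to investigate the ability of acupuncture to prevent the occurrence of cerebral vasospasm has been conducted". It adds that there has been no randomized trial of acupuncture for this condition.

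On incidence, the Background states: "Vasospasm occurs in 50 to 70% of SAH patients, and about 50% of these patients suffer neurological symptoms", and it then names those symptoms as DIND.

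**The concern.** Two separate things weaken the power statement.

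First, the stated power does not follow from the stated inputs. Anyone who puts 38.9%, 10%, two-sided 5% and 95% into the printed formula obtains a much larger number than 39.

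Second, the inputs are less firm than the section suggests. A pilot trial reads as prospective evidence, whereas by the document's own account the 28.9-point difference is a non-randomized, retrospective comparison. The control rate also sits above the range that follows from the Background, and the section does not comment on the gap.

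At stake is how a non-significant primary result will be read. Readers told that the trial had 95% power will take such a result as stronger evidence against the planned effect than the design can provide.

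**Working it through.** **Inputs.** Control rate 0.389, study rate 0.10, two-sided 5%, 95% power, 20% dropout and 39 per arm (Sample size estimation); 80 patients in total (Participants). Equal allocation is assumed, since one number per arm is given. The planned relative risk is 0.10/0.389 = 0.257.

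**1. The plan's own figure.** The formula is n = (z_α/2 + z_β)² (p_c q_c + p_t q_t)/(p_c − p_t)².

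- Variance term: 0.389 × 0.611 + 0.10 × 0.90 = 0.2377 + 0.0900 = 0.3277.
- Squared difference: 0.289² = 0.0835.
- At 95% power: (1.960 + 1.645)² = 12.99, so n = 12.99 × 0.3277/0.0835 = 50.98. That is 51 evaluable, and 51/0.8 = 63.75, so 64 randomized per arm (128 in total).
- At 80% power: (1.960 + 0.842)² = 7.85, so n = 30.79. That is 31 evaluable, and 31/0.8 = 38.75, so 39 randomized per arm.

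The printed 39 is therefore matched at 80% power. Other forms do not rescue the 95%: the pooled version needs 55 evaluable and 69 randomized per arm, and the continuity-corrected version needs 62 and 78. A one-sided test with the printed formula still needs 54 randomized.

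**2. Power of the planned 80 patients at the planning rates.** Power = Φ(|p_c − p_t|/√[(p_c q_c + p_t q_t)/n] − 1.96).

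- 32 evaluable per arm (40 less 20%): Φ(2.856 − 1.960) = 81.5%.
- 40 per arm: Φ(3.193 − 1.960) = 89.1%.

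The formula is not conservative. Fisher's exact test, one of the two tests that the statistical analyses section allows for such outcomes, gives 70% at 31 per arm and 81% at 39 per arm for the same rates.

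**3. The rate implied by the Background.** 50% × 50% = 25% and 70% × 50% = 35%. The planned 38.9% is 3.9 points above the top of this range and 13.9 above the bottom.

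**4. Power across control rates, planned relative risk kept.**

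| Control rate | Study rate | 32 per arm | 40 per arm |
|---|---|---|---|
| 25% | 6.4% | 56% | 66% |
| 30% | 7.7% | 66% | 76% |
| 35% | 9.0% | 75% | 84% |
| 38.9% | 10.0% | 81.5% | 89% |

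**5. Separating the two losses.** From the claimed 95%, the calculation itself loses 95 − 81.5 = 13.5 points at 32 per arm, or 95 − 89.1 = 5.9 at 40 per arm, before any input is questioned. Moving the control rate from 38.9% to 35% then costs 81.5 − 75.3 = 6.2 points, or 89.1 − 84.1 = 5.0. Moving it to 25% costs 81.5 − 56.0 = 25.5 points, or 89.1 − 65.6 = 23.5.

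**The case against.** A reader might infer that the high control rate is why 95% power fails. The documents do not support that: the 95% is already missed at 38.9% against 10%, and would be missed if nobody questioned those rates. The effect of the inputs alone is modest near 35% and large only near 25%.

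The 25 to 35% range is also a soft benchmark. The document never prints it; it is the product of a broad range and an approximate half. Nor is it a strict ceiling. The Background counts DIND among patients with vasospasm, while the primary outcome section defines it as an unexplained new focal deficit without requiring vasospasm (the Assessment section does add angiographic or Doppler findings). Planning from the team's own data instead of general literature is a legitimate judgement.

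A reader might also infer that the earlier study was deliberately upgraded to a pilot trial. Nothing shows intent: the abstract and Background openly call it retrospective, and the label changes no number. How far its rates may be biased or imprecise cannot be judged from this document, and leaving its group sizes to the cited source is ordinary for an article.

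Finally, the analysis is by intention to treat, so 40 per arm is as relevant as 32 if outcomes are known for everyone randomized. Also, a non-significant result does not prove absence of effect at any of these powers, and 95% confidence limits are planned.

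All of this stands. It limits the input argument to a sensitivity range and a wording correction. It does not restore the 95%.

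**Conclusion.** The 95% power figure is wrong as written. With the section's own formula and rates, 39 per arm corresponds to 80% power, and 80 patients give 81.5 to 89% depending on dropout. This part rests only on printed inputs and equal allocation.

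The second part is weaker but holds. The lower power still depends on a non-randomized source described inconsistently, and on a control rate modestly above what the Background implies. Over control rates of 25 to 35% power is 56 to 75% at 32 per arm and 66 to 84% at 40 per arm, assuming that the planned relative risk of 0.257 applies at every control rate. If the study rate instead stayed at 10%, the effect would shrink and power would be lower (44%, 64% and 80% at 40 per arm for 25%, 30% and 35%), but no section of the document supports that assumption over the other. None of these scenarios reaches 95%.

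**What to change.** In Sample size estimation:

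- Describe reference 24 as the Background does, as a retrospective and non-randomized study.
- Replace the 95% with the power of the planned 80 patients at the planning rates: about 81.5% after 20% dropout and 89% without dropout.
- Add one sentence giving the power over control rates of 25 to 39%, stating whether the relative risk or the study rate is held fixed.

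This takes two or three sentences and leaves enrolment unchanged. The cost is a less favourable stated power. If 95% really is intended, the section would have to state 64 per arm, which is a different trial size from the one planned.

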### Participants

#### Subject enrollment, randomization, and blinding

A total of 80 participants will be recruited for this trial. Patients with SAH admitted to our hospital are potential candidates for the study. Eligible participants will be randomized to the study group or the control group after written informed consent is obtained. Concealed allocation will be achieved by randomization and allocation by an assigned researcher without patient contact. Randomization will be done using a computer-generated allocation list by an assigned researcher not involved in the intervention or assessment. Stratified block randomization will be carried out according to sex and the Hunt and Hess Scale (HHS) [25]. The physician involved in the intervention will receive a random number by phone after the informed consent form has been signed and the HHS has been evaluated. A flow chart of the study is presented in Figure 1.

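### The stated 95% power does not go with 39 per arm: the plan's own formula gives 39 at 80% power and 64 at 95%

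*Protocol article*

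**What the plan says.** The article sizes the trial on its primary outcome: "DIND, the primary outcome of the trial, was used to calculate the sample size". The event rates come from the sponsor's own pilot: "the incidence rate of DIND was 10% in the study group and 38.9% in the control group", a difference of 28.9 percentage points. The section then states the result: "To detect this difference with a two-sided 5% significance level and a power of 95%, 39 participants per intervention arm have to be randomized". The 39 already includes the loss to dropout: "39 participants per intervention arm have to be randomized, allowing for a 20% dropout rate". A two-proportion formula with unpooled variances is printed directly below. The enrolment section gives the total: "A total of 80 participants will be recruited for this trial", which fits 2 × 39 = 78 rounded up.

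**The concern.** Every input, the formula and the result are printed together, so the claim can be checked from that one section. A difference of 28.9 points is large, but 39 randomized per arm leaves only about 31 evaluable after 20% dropout, which looks too few for 95% power.

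The statement describes what the trial can show on its primary outcome. Taken at face value, a non-significant result from 80 patients would carry only a 5% chance of having missed the target effect. If the true power is nearer 80%, that chance is about four times larger, and a null result would be given more weight than the design supports.

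**Working it through.** **Inputs, all from Sample size estimation:** control rate p_c = 0.389; study-group rate p_t = 0.10; two-sided alpha 5% (z = 1.960); stated power 95% (z = 1.645); dropout 20%; stated result 39 per arm.

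**Formula as printed:** n = (z_α/2 + z_β)² × (p_c q_c + p_t q_t) / (p_c − p_t)².

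- Sum of variances: 0.389 × 0.611 + 0.10 × 0.90 = 0.3277.
- Squared difference: 0.289² = 0.0835.
- Dropout: divide the evaluable number by 0.8 and round up.

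**Reproducing the plan's 39.** At 80% power (z_β = 0.842), (1.960 + 0.842)² = 7.849. Then 7.849 × 0.3277 / 0.0835 = 30.8, rounded up to 31. 31 / 0.8 = 38.75, rounded up to **39**, the stated figure.

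**At the stated 95% power.** (1.960 + 1.645)² = 12.995. Then 12.995 × 0.3277 / 0.0835 = 50.98, rounded up to 51. 51 / 0.8 = 63.75, rounded up to **64 per arm, 128 in total**.

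| Power | n by formula | Evaluable per arm | Randomized per arm |
|---|---|---|---|
| 80% | 30.8 | 31 | 39 |
| 85% | 35.2 | 36 | 45 |
| 90% | 41.2 | 42 | 53 |
| 95% | 50.98 | 51 | 64 |

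**Could another convention give 39 at 95% power?** None of those tried does, and each exceeds 39 even before dropout is added:

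- one-sided alpha, unpooled: 43 evaluable, 54 randomized;
- two-sided, pooled variance: 55 and 69;
- two-sided, continuity-corrected: 62 and 78;
- printed formula, with dropout added as 20% of n instead of dividing by 0.8: 51 × 1.2 = 61.2, so 62 randomized.

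**Power the planned numbers deliver.** The formula column is Φ(0.289 / √(0.3277/n) − 1.960). The other two columns are exact enumerations for the two tests named in Statistical analyses.

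| Analysed per arm | Printed formula | Chi-square, exact power | Fisher's exact test |
|---|---|---|---|
| 31 (39 less 20%) | 80.3% | 78.7% | 69.5% |
| 32 (40 less 20%) | 81.5% | 80.3% | 71.7% |
| 39 (no loss) | 88.4% | 87.5% | 81.4% |
| 40 (no loss) | 89.1% | 88.2% | 82.7% |

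No cell reaches 95%.

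**Sensitivity to the control rate (a side point).** The Background says: "Vasospasm occurs in 50 to 70% of SAH patients, and about 50% of these patients suffer neurological symptoms". That implies DIND in 0.50 × 0.50 = 25% to 0.70 × 0.50 = 35% of patients. Assume the pilot's relative risk, 0.10 / 0.389 = 0.257, stays constant; this assumption is not in the article. The printed formula with 32 per arm then gives power of 56%, 66% and 75% at control rates of 25%, 30% and 35%.

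**The case against.** The arithmetic is not open to dispute, but four points limit what follows from it.

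- **The article never mentions 80%.** That it was the power used is inferred from the exact match. A pooled-variance formula at 85% power can also give 39: two-sided before dropout, or one-sided after it. So the match is strong evidence, not proof. This stands. What is proved is that 95% and 39 are incompatible.
- **All randomized participants are to be analysed**, according to Statistical analyses. If every outcome is obtained, 40 per arm gives a type II error of about 11% by the formula, not 20%. This also stands, but it does not rescue the claim: 11% is still more than twice the stated 5%, and the plan itself allows for 20% loss.
- **The figure of 80% is not assured under every permitted test.** Fisher's exact test with 31–32 per arm gives 70–72%. This is correct, and it points further away from 95%.
- **The Background rates are general figures**, while the plan relies on its own pilot, and the sensitivity figures need the constant relative risk. They are useful context, but the error does not depend on them.

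The error leaves the type I error, the randomization and the effect estimate untouched, and the planned 95% confidence limits will show the imprecision whatever power was stated.

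**Conclusion.** The power statement is wrong as written. With the plan's own rates, alpha, formula and dropout allowance, 95% power needs 64 randomized per arm (128 in total), which is 60% more than the planned 80. The stated 39 is what that formula gives at 80% power. The planned type II error is therefore about 20% if dropout runs as assumed, and about 11% by the formula if all 80 are analysed; in neither case is it 5%. These figures take the pilot rates of 38.9% and 10% as true. Nothing elsewhere in the article resolves the conflict, and a separate analysis plan could not make the sentence true.

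**What to change.** In Sample size estimation, change the stated power from 95% to 80%, and add that analysing all 80 patients would give about 89% by the same formula. This fits the planned total of 80 and leaves recruitment, treatment and analysis unchanged. The sponsor should confirm that 80% was intended. If 95% was, the sample size has to be corrected instead, to 64 per arm.

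Optionally, give the power at control rates of 25%, 30% and 35% and state the constant relative risk as an assumption.

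The cost is a one-line correction, repeated wherever else the power is quoted, and a less favourable stated power.

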### Dropout criteria

Participants conforming to any of following conditions will be removed from the study: (1) more than three sessions (out of a total of 12) are not performed; (2) withdrawal of patient consent; (3) severe adverse events making the trial unsustainable; (4) worsening condition making it difficult to participate in the trial; or (5) impractical to continue with the trial, as judged by the principal investigator.

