### Statistical analyses

According to the principle of intention-to-treat, all randomized participants will be analyzed using SPSS version 18.0 (SPSS Inc., Chicago, IL, USA) software. All data will be represented as mean ± standard deviation (SD) or number (%). For comparisons of two groups, an independent samples *t*-test or Mann- Whitney *U* test will be used for continuous outcomes, and a χ^2^-test or Fisher’s exact test will be used for noncontinuous outcomes. To control for possible confounding factors (for example, age, Hunt and Hess Scale, modified Rankin Scale, *etcetera*), multiple regression analysis will be performed for the comparison of two groups. Confidence limits of 95% will be calculated and *P* values of < 0.05 will be considered statistically significant.

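### The dropout allowance, the removal rule and the intention-to-treat analysis do not agree, and the printed 95% power is not reached on any reading of them

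*Protocol article*

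**What the plan says.** Three sections of the protocol article bear on patients who drop out.

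- **Sample size estimation.** From the earlier study, "the incidence rate of DIND was 10% in the study group and 38.9% in the control group". The calculation is made "with a two-sided 5% significance level and a power of 95" per cent, and the result is that "39 participants per intervention arm have to be randomized, allowing for a 20% dropout rate". The Participants section rounds the total up: "A total of 80 participants will be recruited for this trial", or 40 per arm if allocation is equal.
- **Dropout criteria.** "Participants conforming to any of following conditions will be removed from the study". The conditions include that "more than three sessions (out of a total of 12) are not performed", as well as withdrawn consent, severe adverse events, a worsening condition and the principal investigator's judgement.
- **Statistical analyses.** "According to the principle of intention-to-treat, all randomized participants will be analyzed".

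Nothing in the document says whether DIND is still recorded for a patient after removal, or what outcome such a patient would carry into the analysis.

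**The concern.** An allowance of the form n/(1 − d) restores the sample when a share d of patients yields no outcome. It presumes that the remaining patients show the full planned difference. The removal rule fits that presumption, but the analysis statement does not. If every randomized patient is analysed, dropouts are no longer a loss of sample size. They enter the comparison, and those in the study arm may not have the 10% rate assumed for that arm. If instead their outcomes are not collected, the promise to analyse everyone cannot be met from observed data.

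At stake is the power figure against which the result will be read. A null result judged against 95% power would look like stronger evidence against acupuncture than this design can give.

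**Working it through.** **Inputs.** From Sample size estimation: p_c = 0.389, p_t = 0.10, two-sided α = 0.05, stated power 95%, dropout 20%, 39 per arm. From Participants: 80 in total, so 40 per arm at equal allocation.

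**Step 1: reproduce the 39.** The protocol's formula is n = (z_α/2 + z_β)² (p_c q_c + p_t q_t)/(p_c − p_t)².

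- Variance term: 0.389 × 0.611 + 0.10 × 0.90 = 0.3277. Squared difference: 0.289² = 0.0835. Ratio: 3.923.
- At 80% power: (1.960 + 0.842)² × 3.923 = 30.79, so 31; 31/0.8 = 38.75, so **39**.
- At 95% power: (1.960 + 1.645)² × 3.923 = 50.98, so 51; 51/0.8 = 63.75, so **64**.

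The printed 39 therefore corresponds to 80% power, and the allowance is division by (1 − 0.20).

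**Step 2: power if dropouts yield no outcome.** Inverting the formula, power = Φ(|p_c − p_t| / √[(p_c q_c + p_t q_t)/n] − 1.96).

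- n = 31: 0.289/0.1028 − 1.96 = 0.851, power **80%**.
- n = 32 (80% of 40): power 81%.

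**Step 3: power if all randomized patients are analysed and dropouts keep the full effect.**

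- n = 39: 0.289/0.0917 − 1.96 = 1.193, power **88%**.
- n = 40: power **89%**.

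**Step 4: power if all are analysed and the effect is diluted.** The document gives no DIND rate for dropouts. As an assumption, let control-arm dropouts keep the 38.9% rate and let the 20% of study-arm dropouts lose some or all of the benefit.

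- Half the benefit kept: dropout rate (0.10 + 0.389)/2 = 0.2445; study-arm rate 0.8 × 0.10 + 0.2 × 0.2445 = 0.129; difference 0.260.
- No benefit kept: study-arm rate 0.8 × 0.10 + 0.2 × 0.389 = 0.158; difference 0.231.

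| Study-arm dropouts keep | 39 per arm | 40 per arm |
|---|---|---|
| full benefit | 88% | 89% |
| half | 78% | 79% |
| none | 66% | 67% |

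For the last row, exact enumeration gives 65% for the chi-square test at either size, and 55% (39 per arm) or 57% (40 per arm) for Fisher's test. The protocol allows either test. For the first row the exact figures are 88% for chi-square at either size, and 81% (39 per arm) or 83% (40 per arm) for Fisher.

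**Step 5: where dilution starts to matter.** At 39 per arm, power equals the 80% behind the calculation when about 43% of study-arm dropouts take the control rate: p_t = 0.10 + 0.2 × 0.43 × 0.289 = 0.125, difference 0.264, z = 0.264/0.0943 − 1.96 = 0.84. Below that share, keeping dropouts in the analysis raises power above 80%; above it, power falls short.

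**The case against.** A reader might infer that dropouts certainly stay in the analysis, dilute the effect and bring power down to about 66%. The document does not support that.

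- The dropout section removes these patients, and no section says their DIND status is still collected. If it is not, dividing by 0.8 is the usual allowance. Dilution is therefore a possibility, not a stated feature of the design.
- The no-benefit case is an extreme. A patient who misses four of the 12 sessions is a dropout after receiving eight, and the Background puts the peak of vasospasm at days 7 to 10.
- The article does not say whether the earlier study's 10% rate excludes incompletely treated patients. If it already includes them, the dilution above is counted twice and the 88 to 89% figure is the relevant one.
- Relative to the 80% that generates 39, the intention-to-treat analysis changes power by anything from about +8 to −14 points at 39 per arm.

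It would also be wrong to blame intention-to-treat for the whole gap from 95%. With no dropout loss and no dilution, 39 per arm gives 88%. That shortfall comes from a separate error: the number was computed for 80% power and printed as 95%.

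Combining n/(1 − d) with an intention-to-treat analysis is common, and detailed rules for missing outcomes may sit in a document not shown. The planned 95% confidence limits also offer some protection against over-reading a null result. All of this stands and limits the point. It does not remove it, because the allowance, the removal rule and the analysis population are all printed here and conflict.

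**Conclusion.** The point holds as an inconsistency among three statements, together with a power figure that none of their readings delivers. If removed patients have no outcome, power is about 80% (31 evaluable per arm), and the all-randomized analysis cannot be carried out on observed data. If they have outcomes, the allowance corrects for a loss that does not occur, and power is at most 88 to 89%. Lower values, down to 66 to 67%, depend on an assumed loss of benefit among study-arm dropouts that the document neither states nor excludes. All figures take the protocol's 38.9% and 10% rates and 20% dropout as given.

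The inconsistency would remain if the 95%/80% mismatch were corrected by itself. At 64 per arm, all analysed, power is 98% with full benefit, 94% with half and 86% with none.

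**What to change.** - **Sample size estimation:** replace 95% with the power of the intention-to-treat analysis of the 80 randomized patients. State it as at most about 89%, about 79% if study-arm dropouts keep half the benefit and about 67% if they keep none, and say that the last two rest on an assumption. Any 80% figure should be labelled as the power with 31 completers per arm.
- **Dropout criteria and Statistical analyses:** reconcile the two by separating stopping the intervention from leaving follow-up. Say that patients who stop the intervention continue to be followed for DIND, unless they withdraw consent, and are analysed in their randomized group. DIND is already recorded and verified daily under the primary outcome, so this uses an existing procedure.

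The cost is one restated paragraph and one clarifying sentence. No additional enrolment is proposed. The only drawback is a less favourable stated power.
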